### Baseline measures

After signing the informed consent form, eligible participants will complete baseline questionnaires. These questionnaires will gather demographic information, including age, relationship status, field of study, university, academic program, academic performance, employment status, socioeconomic status, and health history, as part of the demographics and health history questionnaire. Additional questionnaires will assess cognitive reserve [78], personality traits [79], and participants’ expectations regarding treatment outcomes. To estimate general intelligence, the Vocabulary and Matrix Reasoning subtests from the Wechsler Adult Intelligence Scale–III (Wechsler, 2001) will be included in the baseline neuropsychological evaluation [80].

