### Statistical analyses

Data will be entered into a version-controlled Excel database. Analyses will be conducted using the latest available versions of IBM SPSS Statistics and R. A two-tailed p-value < 0.05 will denote statistical significance, with adjustments for multiple comparisons applied where appropriate. Descriptive statistics (means, standard deviations, medians, ranges, and frequencies) will summarize baseline characteristics overall and by group. We will assess distributional assumptions, including skewness and the presence of outliers. Missing data will be characterized by reporting the percentage of missing values for each variable and by evaluating the most likely mechanisms, classified as missing completely at random (MCAR), missing at random (MAR), or missing not at random (MNAR).

Primary hypotheses will be tested under an intention-to-treat (ITT) framework, including all randomized participants. Analysis of covariance (ANCOVA) will model change scores (post-intervention – baseline) using group, baseline score, and selected covariates as predictors. Sex and age will be included as covariates in all analyses. Additional covariates will be considered from a pool of theoretically relevant candidates if they show a significant and meaningful association with the outcomes. To minimize multicollinearity, we will examine the interrelationships among selected predictors and retain only one variable when substantial overlap is observed. If the omnibus test is significant, we will perform pairwise comparisons within each outcome variable using appropriate corrections for multiple comparisons (e.g., Bonferroni). Assumptions of homogeneity of regression slopes, normality, and homoscedasticity of residuals will be checked. If violated, alternative models (e.g., mixed-effects models for repeated measures) will be considered. Between-group findings will be supplemented by within-group analyses (paired t-tests or Wilcoxon tests, as appropriate).

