Missing outcome data will be handled using multiple imputation by chained equations (MICE), assuming data are MAR. Predictive mean matching will be applied, with the number of imputations and iterations guided by current recommendations [105]. The imputation model will mirror ANCOVA predictors and include auxiliary variables to improve accuracy. We will assess imputation diagnostics (trace plots, distributional comparisons) and pool results using Rubin’s rules. Complete-case analyses and sensitivity tests under MNAR will also be reported. Exploratory analyses will examine adherence as a continuous predictor and test adherence-by-treatment interactions. These models will include the same set of covariates used in the primary ANCOVA analyses to ensure comparability. Mediation and moderation effects will be tested using Hayes’s PROCESS macro with a minimum of 5,000 bootstrap samples. Given the proof-of-concept nature of Study 2, effect sizes (partial eta squared for ANCOVA) will be reported to aid interpretation of the findings.

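### The exploratory adherence models reuse a covariate set screened on the outcome, so modest baseline confounders of adherence may go unadjusted

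*Protocol article*

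**What the plan says.** All of this is in the Statistical analyses section of the protocol article unless stated otherwise.

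- **Adherence analysis.** "Exploratory analyses will examine adherence as a continuous predictor and test adherence-by-treatment interactions". Its covariates are then fixed: "These models will include the same set of covariates used in the primary ANCOVA analyses to ensure comparability".
- **The primary set.** The ANCOVA models change scores "using group, baseline score, and selected covariates as predictors". "Sex and age will be included as covariates in all analyses". Beyond these: "Additional covariates will be considered from a pool of theoretically relevant candidates if they show a significant and meaningful association with the outcomes". A second filter for collinearity will "retain only one variable when substantial overlap is observed". The candidate pool is not listed.
- **What adherence is.** Under Intervention adherence, it is session attendance plus total time in supervised and independent practice. The independent part is self-reported.
- **What is collected beforehand.** Under Baseline measures, the questionnaires cover "academic performance, employment status, socioeconomic status, and health history", as well as personality traits and expectations about treatment outcomes.

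**The concern.** In the primary ANCOVA the group effect is protected by randomisation. Covariates there mainly buy precision, and choosing them by association with the outcome does little harm. Adherence is different: it arises after randomisation and each student chooses it. Students with more time, or with higher expectations, may practise more and may also improve more for other reasons. A covariate set that suffices for the arm comparison need not suffice for the adherence slope, so comparability is a weak reason to tie the two together.

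The selection rule looks only at the outcome, and through a significance test. A variable with a modest link to the outcome will often fail that test at this sample size, and the collinearity filter can remove another. Several such variables, each dropped alone, can together bias the slope. The project gives adherence a prominent place: the second Study 2 hypothesis pairs better adherence with greater benefit, and the Discussion names busy schedules and exams as obstacles. A slope that partly reflects who practises could therefore be read as an effect of practising.

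**Working it through.** **1. The plan's own figure.** No figure is stated for the adherence models. The sample size reproduces: noncentrality N·f² = 159 × 0.25² = 9.94 on (2, 156) degrees of freedom gives critical F = 3.054 and power 0.805; 159/0.9 = 176.7, rounded up to 177. I use n = 159, in three equal groups, with two-sided α = 0.05.

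**2. Assumed inputs.** The documents give no correlation of any baseline variable with adherence or outcome. I take K independent drivers, each with weight a on adherence and b on outcome, and no true adherence effect. "Significant" in the screen is taken as p < 0.05.

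**3. Chance that one driver passes the screen.** Approximately P(Z > 1.96 − b√n), with √159 = 12.61:

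- b = 0.12: P(Z > 0.45) = 0.33
- b = 0.15: P(Z > 0.07) = 0.47
- b = 0.20: P(Z > −0.56) = 0.71
- b = 0.30: P(Z > −1.82) = 0.97

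Simulation agrees where both exist (0.46–0.47, 0.71 and 0.97 for the last three). Of six drivers at b = 0.12, about 6 × 0.33 = 2.0 are kept (simulated 1.9–2.0). Counting all 177 barely changes this: at b = 0.15, P(Z > 1.96 − 0.15 × 13.30) = 0.51.

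**4. Bias if no driver is adjusted for.** With adherence at unit variance the spurious slope is K·a·b. For K = 3, a = 0.30, b = 0.15 this is 0.135 (simulated 0.136). The screen reduces it to 0.051, and including all three drivers gives 0.002.

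**5. False-positive rate of the adherence slope** (1,500–4,000 simulated trials per setting; ranges come from repeat runs; a dash means not reported):

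| Drivers | a | b | Plan's rule | Drivers always in |
|---|---|---|---|---|
| 1 | 0.25 | 0.12 | 5.9% | – |
| 1 | 0.30 | 0.20 | 5.5–6.0% | 5.3% |
| 2 | 0.25 | 0.12 | 7.1% | – |
| 3 | 0.30 | 0.15 | 8.9–10.0% | 4.8–5.3% |
| 4 | 0.15 | 0.12 | 7.2% | – |
| 4 | 0.25 | 0.12 | 9.3–11.5% | 4.7% |
| 6 | 0.15 | 0.12 | 9.1% | – |
| 6 | 0.25 | 0.12 | 16.7–19.7% | 4.8–5.0% |
| 6 | 0.25 | 0.15 | 17.0–18.3% | 5.1–5.2% |
| 6 | 0.30 | 0.10 | 22.8–23.5% | 4.9–5.2% |

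At six drivers, a = 0.25 and b = 0.12, the spurious slope under the rule is 0.09 SD of outcome per SD of adherence, against 0.00 with the drivers in. Some of these runs left out the baseline score. A repeat with it in the model gave about 5% for one or two modest drivers, 7–9% for three or four and 18% for six, against about 4–5% with the drivers forced in.

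**6. Where no harm arises.** One driver with a = 0.50 and b = 0 gives 3.9% under the rule. One with a = 0.50 and b = 0.30 is selected in 97% of runs and gives 4.6%.

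**7. Sensitivity.** The rule also asks for a meaningful association but gives no threshold. If that meant a coefficient of at least 0.2, three drivers at 0.30/0.15 would give 16.9% instead of 8.9%. With p < 0.05 alone, three drivers at 0.50/0.15 give 18.5%, but they would explain 3 × 0.50² = 75% of adherence variance.

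The adherence-by-treatment terms were not simulated. If confounding acted equally in all arms, the spurious slopes would be equal and the interaction would stay near zero. It is distorted to the extent that the drivers act differently by arm.

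**The case against.** A reader might infer that the plan leaves the drivers of adherence out and that a false dose-response will follow. The documents do not support that:

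- The candidate pool is not listed, and an article may leave that list to a fuller document. Expectations, personality, employment and academic performance are neither assured of entry nor excluded.
- Confounding needs a link to the outcome as well as to adherence. A driver unrelated to the outcome is harmless when omitted, and one strongly related to it will usually be selected.
- Baseline score, sex and age are already in the model, so confounding through baseline distress is largely addressed in the distress models.
- The analysis is labelled exploratory, nothing calls its slope causal or a dose-response, and the Study 2 hypothesis compares VR with non-VR delivery rather than resting on this slope.

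The magnitude can also be challenged. The higher rates need six independent drivers all pushing the same way. At a = 0.25 they explain 6 × 0.25² = 37.5% of adherence variance, and at 0.30 they explain 54%, which is a lot to ask of baseline questionnaires. The return to 5% is partly by construction, because the only confounders simulated are those then forced in. Motivation and exam load are not listed among the baseline measures and would remain.

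These points stand, and they limit the size and certainty of the problem. They do not rescue the rule itself, which the article states outright: the covariate set is fixed by a screen in which adherence plays no part, and comparability is the only reason given.

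**Conclusion.** The point holds in a limited form. Tying the adherence models to the primary covariates may leave residual confounding in the adherence slope and, where the drivers act differently by arm, in the adherence-by-treatment terms. The risk comes from several modest confounders that each fail the screen, not from any single strong one.

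Under the assumed correlations, a null slope is declared significant in about 5–7% of trials with one or two weak drivers and 7–12% with three or four at weights up to 0.30. With six it is about 17–24% at adherence weights of 0.25–0.30, and 9% at 0.15. Always including the drivers gives about 5%, for measured confounders only. These figures rest on correlations that the documents do not give and on a p < 0.05 reading of the screen. The primary intention-to-treat comparison is unaffected. Severity is minor.

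**What to change.** Replace the sentence on covariates in the adherence models by:

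> Adherence models will include the primary ANCOVA covariates plus, regardless of significance, prespecified baseline variables expected to affect both adherence and outcome (expectations, personality traits, employment status, academic performance). The model with primary covariates only will be shown beside it, and results will be reported as associations.

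Showing both models keeps the comparability that the plan wants. Reporting associations acknowledges that unmeasured motivation remains.

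The cost is wording and a few degrees of freedom in an exploratory model. With intercept, two group terms, baseline score, sex, age, adherence and two interaction terms, 159 − 9 = 150 residual degrees of freedom remain; six added terms, for example, would leave 144. All the variables are already collected at baseline, so no new data are needed.

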### Sample size

A power analysis was conducted using G*Power software (version 3.1.9.4) for a one-way ANOVA (fixed effects, omnibus) with three groups. Assuming a medium effect size (f = 0.25), α = 0.05, and a desired power of 0.80, the analysis yielded a required sample size of 159 participants, with a critical F-value of 3.054. To accommodate an expected dropout rate of 10%, the sample size was adjusted using the proportional method, resulting in a final target of 177 participants (59 per group). This adjustment ensures that statistical power remains adequate even if participant attrition occurs. Study 2 will include 45 participants (n = 15 per group) as part of a proof-of-concept trial intended for preliminary exploration. For Study 1, biological samples (fecal) will be collected from a randomly selected subgroup of 90 participants (30 per group) before and after the interventions. Furthermore, a subset of 24 participants (12 from each study) will be selected for the qualitative study using purposive sampling to capture diverse perspectives [67]. The sample size is based on previous studies [56,61,68] and evidence suggesting that qualitative inquiry often reaches data saturation with approximately 12 participants [69].

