Certain practical and operational issues in executing the YoungFitT project require discussion. First, recruiting and retaining participants, as well as ensuring adherence to intervention protocols, presents significant challenges. Engaging university students, who often have busy schedules and exam-related commitments, requires strategic planning and effective communication. To address recruitment challenges, we will implement alternative strategies, including outreach to additional universities and faculties. Our approach also includes offering flexible scheduling options and collecting detailed information about participants’ experiences and any obstacles they encounter in maintaining engagement. Furthermore, as Study 2 is an exploratory proof-of-concept study, the relatively small sample size may limit the ability to detect statistically significant between-group differences. Therefore, the findings will be considered preliminary and are primarily intended to inform the design and implementation of future, larger-scale investigations. Finally, the implementation of VR-based interventions may present technical difficulties. Technical support from IT personnel and timely equipment replacement will help mitigate these challenges.

In conclusion, our goal is to ensure the smooth execution of the YoungFitT project and to maximize its impact on enhancing the mental and physical health of students through innovative physical exercise and mind-body interventions. This effort aims to provide valuable insights that can guide future approaches to promoting student well-being throughout their academic and professional journeys.

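### Study 2 reports partial eta squared, which at N = 45 is biased upward by about 0.05 and shows neither direction nor arm

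*Protocol article*

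**What the plan says.** The Sample size section states that "Study 2 will include 45 participants (n = 15 per group) as part of a proof-of-concept trial intended for preliminary exploration". It gives no power or precision figure for that study.

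Under Statistical analyses, "Analysis of covariance (ANCOVA) will model change scores (post-intervention – baseline) using group, baseline score, and selected covariates as predictors", and "Sex and age will be included as covariates in all analyses". Further covariates may be added. On contrasts between arms: "If the omnibus test is significant, we will perform pairwise comparisons within each outcome variable". Within-group tests supplement the between-group results and do not depend on the omnibus test. For Study 2 specifically, and because it is a proof-of-concept study, "effect sizes (partial eta squared for ANCOVA) will be reported to aid interpretation of the findings".

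The Discussion concedes that Study 2 may be too small to detect differences between groups, and adds that "the findings will be considered preliminary and are primarily intended to inform the design and implementation of future, larger-scale investigations".

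Under Objectives and hypotheses, the Study 2 hypotheses are specific to each arm: cognitive gains for HIFT, psychological gains for MBSR, and moderate benefits for QG.

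**The concern.** Sample partial eta squared is a proportion of variance, so it cannot fall below zero, and chance differences between arms always push it upward. The excess is roughly the effect degrees of freedom divided by the sample size. It is negligible in a large trial but not with 45 participants. The protocol chooses this index because Study 2 is small, and a small sample is where the index performs worst.

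Calling the findings preliminary warns a reader about imprecision. It does not warn about an error in a known direction.

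The index also comes from a three-group omnibus test, so it says neither which arm did better nor by how much. The Study 2 hypotheses ask exactly that. If the omnibus test is not significant, the stated plan supplies no between-arm contrast. What remains is this one undirected number and the within-group tests.

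**Working it through.** **Inputs.** N = 45 and three arms (Sample size). ANCOVA with group, baseline, sex and age (Statistical analyses), assumed to be the Study 2 model. Medium effect and error rates from the Sample size section: "Assuming a medium effect size (f = 0.25), α = 0.05, and a desired power of 0.80". Group df = 3 − 1 = 2. Error df = 45 − 3 − 3 = 39.

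**The plan's own figure first.** Noncentral F with 2 and N − 3 df and λ = N f². At N = 159 and f = 0.25 the critical F is 3.054 and power is 0.805. Then 159/0.9 = 176.7, rounded up to 177. The Study 1 calculation reproduces. On the variance-explained scale, f = 0.25 is 0.0625/1.0625 = 0.0588.

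**No true effect, Study 2.** Partial eta squared follows a Beta(df1/2, df2/2) distribution, here Beta(1, 19.5).
- Mean = 2/(2 + 39) = 2/41 = 0.049.
- Median = 1 − 0.5^(1/19.5) = 0.035.
- 95th percentile = 1 − 0.05^(1/19.5) = 0.142.
- P(value > 0.0588) = (1 − 0.0588)^19.5 = 0.307, about 31%.

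**Sensitivity of the null mean.** With no covariates it is 2/44 = 0.045, and with two extra covariate df 2/39 = 0.051. If only 40 were analysed, it is 2/36 = 0.056. The figure of 40 is an assumption that borrows Study 1's 10% dropout rate. The planned analysis imputes missing outcomes, so it would apply only to a complete-case analysis.

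**Non-zero effects at N = 45, 39 error df** (simulated from noncentral chi-square draws with λ = N f²):

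| True value | f | Mean partial eta squared | Mean omega squared |
|---|---|---|---|
| 0 | 0 | 0.049 | 0.000 |
| 0.0099 | 0.10 | 0.059 | 0.010 |
| 0.0588 | 0.25 | 0.108 | 0.057 |
| 0.138 | 0.40 | 0.186 | 0.134 |

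Simulation runs differ only in the third decimal (0.107 to 0.108 in the third row). The excess is about 0.05 in every row. At N = 159 with the same covariates it is about 0.013.

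**Chance of reaching the pairwise step.** Omnibus power at N = 45 and f = 0.25 is 0.28, with or without the three covariate df (f taken on the residual scale). In about 72% of such studies no pairwise contrast would follow.

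**Illustration of reuse, not something the protocol plans.** Suppose the average observed value were entered into the one-way ANOVA method used for Study 1.
- Truth f = 0.25, planning on 0.108: about 83 participants instead of 158, with actual power of about 50%.
- Truth f = 0.10, planning on 0.059: about 157 instead of 967, with actual power of about 18%.

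**The case against.** The strongest reply is that this is a conventional descriptive statistic in an exploratory study. Its stated purpose is to aid interpretation. The findings are labelled preliminary, and Study 2 also yields usability, adherence and acceptability data that can inform a larger trial. The index correctly describes the sample, and anyone given F and its degrees of freedom can convert it to omega or epsilon squared.

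Most of this stands, and it limits the point. A reader might infer that the sponsor will size the next trial from this value. No section says so; the harm arises only if the raw figure is read or reused without correction. A reader might also infer that mean differences and confidence intervals will not be reported. The article does not say that either, and a fuller analysis plan may provide them, so their absence here is not the finding. The finding is the index that was chosen and the gate on pairwise contrasts, both of which are stated.

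The reply is also right that omega squared is no cure. Its mean is close to the truth only if negative values are kept. Under no effect about 62% of values are at or below zero, and setting those to zero raises the mean to 0.017. It still exceeds 0.0588 in about 10% of null studies. At a true 0.0588 its standard deviation is about 0.077, against 0.079 for partial eta squared.

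The within-group tests are not gated, but they do not compare arms and so do not fill the gap.

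**Conclusion.** The point holds as a minor one. At N = 45 the named index overstates the population value by about 0.05. That is nearly the whole of the protocol's medium effect, and it almost doubles such an effect when one is present. In proportion it matters less for large effects (0.186 against 0.138). The index cannot address the arm-specific hypotheses, and the contrasts that could are reached only about 28% of the time at f = 0.25.

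This rests on the general ANCOVA applying to Study 2 with baseline, sex and age as its only covariates, on all 45 being analysed, and on the usual normal-error assumptions. Fewer participants or more covariates make the bias slightly larger. The documents do not support the stronger claim that later trials will be misled. They support only that the value could mislead, given the stated aim of informing larger studies.

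**What to change.** In the Study 2 part of Statistical analyses:
- State that adjusted between-arm mean differences with 95% confidence intervals will be reported for each outcome, whatever the omnibus result.
- If a variance-explained index is wanted, report omega or epsilon squared with its interval, without setting negative values to zero, instead of or beside partial eta squared.
- Add that raw partial eta squared from Study 2 is not to be used for sample-size planning.

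The fitted model and the data are unchanged, so the cost is wording. Reported effects will look smaller and the intervals will be wide. A bias-adjusted point estimate remains imprecise at this sample size and should be read with its interval.

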### Qualitative data analysis

We will conduct thematic analysis to systematically identify, code, and analyze themes and subthemes emerging from the interview data [105]. The analysis will focus on participants’ experiences and perceptions of the interventions. NVivo software will be used for data organization and coding. To enhance analytical rigor, independent coding will be conducted by at least two researchers, with discrepancies resolved through discussion. Representative quotes will be selected to illustrate key themes, ensuring that findings are grounded in participants’ narratives. Data will be interpreted in relation to the broader study objectives, providing insights into participants’ perspectives on the effects of the intervention.

